### Research team

In order to gauge the progress of the study, the NTD research team met monthly to review implementation and evaluation procedures. During the course of the study, the overall research team met quarterly to discuss analysis and results of the study.

### Data collection

Processes and outcomes of NTD include data gathered from residents, families, care teams, and the organization (Table 2). Measures for the residents included quality of life, quality of life for people with ADRD, enhanced care experiences, resident centredness and choice and control, satisfaction with NTD*,* and functional and cognitive status indicators (Selected items from the Minimum Data Set –LTC 2.0) (Table 3). Family measures included proxy quality of life indicators, enhanced care experiences, involvement in care and decision making, and satisfaction with NTD. Measures for the team included beliefs and actions, perception of role enactment and team functioning, continuity in assignments, enhanced care experiences, staff-resident relationships and job satisfaction. Organizational descriptors included work distribution, staff turnover and retention. Data were collected through observations, interviews, focus groups, surveys, medical record and chart reviews, and database reviews. Data were collected between March 2013 and March 2017. Data analysis and manuscript writing is ongoing.

**Table 2 Tab2:** Variables and Measurement Schedule

Sample	Category	Variables	Measurement Schedule
Resident	Demographics	Age, gender, marital status, unit	All assessments
	Quality of life indicators	Quality of Life Scales for Nursing Home Residents by Kane	Baseline and every 6 months
	Quality of life for people with ADRD	Observing Quality of Life in Dementia (OQOLD) Measure	baseline and every 6 months
	Resident centredness	CARE Profile	baseline and every 6 months
	Resident’s choice and control	Health-Related Quality of Life Measure	Baseline and every 6 months
	Functional and cognitive status	Depression Rating Scale, Index of Social Engagement, weight, CHESS scale, feeding tube, VAS Pain Scale, pressure ulcers (BWAT), physical restraint use, Activities of Daily Living (ADL Self-Performance Hierarchy Scale), indwelling catheter use, dlirium symptoms (CAM), number of falls, UTIs, new infections, use of anti- psychotics and anti- depressants, number of acute care admissions	Baseline and every 6 months
	Semi-structured interviews	Experiences related to the NTD program implementation	Every 12 months
Staff	Demographics	Position, proportion of time spent with residents, employment status (i.e. full-time, part-time, casual), shift type (i.e. day, evening, night), education, years worked in NH, years worked at current NH

**Table 3 Tab3:** Measurement Tools

Scale	Scores	Reference
Cognitive Performance Scale (CPS)	The CPS showed substantial agreement with the MMSE in the identification of cognitive impairment; the sensitivity was .94 (95% confidence interval [CI]: .90, .98), the specificity was .94 (95% CI: .87, .96), and the diagnostic accuracy as measured by the area under the receiver operating characteristics (ROC) curve was .96 (95% CI: .88, 1.0).	Hartmaier, S.L., Sloane, P.D., Guess, H.A., Koch, G.G., Mitchell, C.M., & Phillips, C.D. (1995). Validation of the minimum data set cognitive performance scale: Agreement with the mini-mental state examination. *Journals of Gerontology Series A: Biological Science and Medical Science, 50*, M128–33.
Depression Rating Scale (DRS)	Correlations of 0.69 with Cornell scale and 0.70 with Hamilton Depression Rating Scale. More sensitive and specific than 15-item Geriatric Depression Scale (AUC > 0.80).	Burrows, A.B., Morris, J.N., Simon, S.E., Hirdes, J.P., & Phillips, C. (2000). Development of a minimum data set-based depression rating scale for use in nursing homes. *Age and Ageing, 29,* 165–72.
Activities of Daily Living (ADL)-long form	Interrater reliability > 0.75, internal consistency is high (Chronbach’s alpha = 0.954).	Morris, J.N., Fries, B.E., & Morris, S.A. (1999). Scaling ADLs within the MDS. *Journals of Gerontology Series A: Biological Science and Medical Science, 54* (11), M546–53.
Activities of Daily Living (ADL) –short form	Interrater reliability > 0.75, internal consistency is high (Chronbach’s alpha = 0.90).	Morris, J.N., Fries, B.E., & Morris, S.A. (1999). Scaling ADLs within the MDS. *Journals of Gerontology Series A: Biological Science and Medical Science, 54* (11), M546–53.
Index of Social Engagement (ISE)	Internal consistency is moderate (Chronbach’s alpha = 0.79).	Mor, V., Branco, K., Fleishman, J., Hawes, C., Phillips, C., Morris, J., & Fries, B. (1995). The structure of social engagement among nursing home residents. *Journals of Gerontology Series B: Psychological Science and Social Science, 50* (1), P1–8.
Pain Scale	Kappa between VAS and Pain was 0.707; variance explained 56%.	Fries, B.E., Simon, S.E., Morris, J.N., Flodstrom, C., & Bookstein, F.L. (2001). Pain in

### Data analysis

The evaluation of NTD consists of analysing findings, which aim to address four main objectives:

#### Objective 1: examining the Fidelity of the program

This objective aims at measuring if NTD is delivered as designed. This is addressed by conducting descriptive analyses of the structured observations of staff-resident and team interactions; the surveys and questionnaires; the description of job enactment; and the resident, team members and family satisfaction surveys (Table 2). The quantitative data on fidelity of the program implementation and the observational data will be analyzed descriptively for each site to determine the extent of variation from the planned implementation. In addition, differences in fidelity will be examined across participating sites, using mixed methods. Qualitative data from the semi-structured interviews will be undergoing a constant comparative analysis and will be reviewed separately by two investigators using NVivo 10. Thematic content emerging from the transcripts using an inductive coding technique will be subsequently organized into categorized concepts. The thematic frameworks emerging from the interviews will assist in understanding factors that may contribute to variation in program implementation across the neighbourhoods**.**

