**Methods:**

The study employed a repeated measure, mixed method design. NTD consisted of a 30-month standardised training and implementation plan to modify the physical environment, organize delivery and services and align staff members to promote inter-professional team collaboration and enhanced resident centeredness. Training was centred in each 32-resident neighbourhood or home area. Quantitative and qualitative data were collected with reliable and valid measures over the course of 3 years from residents (clinical outcomes, quality of life, satisfaction with care, perception of person centeredness, opportunities for social engagement), families (satisfaction with care for relative, person centeredness, relationship opportunities), team members (satisfaction with job, ability to provide person centered care, team relationships) and organizations (retention, turnover, staffing, events) in 6 NHs. Mixed models were used for the analysis.

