### Aims

The goal of this current study was to implement and evaluate NTD. The specific objectives were to: 1. Examine the fidelity of the program when implemented in a multi-home NH organization; 2. Explore contextual factors associated with implementation and outcomes; 3. Examine the effects of the program on residents, team members, family, and organizational outcomes and the association between the level of implementation fidelity and outcomes, and; 4. Determine the mechanisms through which NTD exerts its effects.

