#### Objective 3: examine effects of the program on residents, team members, family, and organizational outcomes, and the association between the level of implementation Fidelity and outcomes

The effect of NTD on outcomes will be measured by conducting a descriptive analysis (including mean, standard deviation and frequencies) of all outcome indicators at each data collection point. Mixed models will be conducted on the quantitative data to examine changes in and resident’, family’, and team member’s outcomes variables over time and between groups, while accounting for possible site differences. Qualitative data from the semi-structured interviews will be undergoing a constant comparative analysis. Organizational data will be analyzed by conducting a descriptive analysis on job descriptions and work distribution, skill mix, supportive organizational systems, and staff turnover and retention. Effect of NTD on residents, team members, family, and organization will be described in the context of program.

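### Satisfaction surveys count as evidence of fidelity and also belong to the evaluation data, so the planned fidelity-outcome association is biased wherever the same survey serves both

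*Protocol article*

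**What the plan says.** The section on Objective 1 states its purpose plainly: "This objective aims at measuring if NTD is delivered as designed". It names four kinds of source. The first is structured observation of staff-resident and team interactions. The others are "the surveys and questionnaires; the description of job enactment; and the resident, team members and family satisfaction surveys", with a reference to Table 2. The quantitative fidelity data are then to be "analyzed descriptively for each site to determine the extent of variation from the planned implementation".

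The Methods paragraph of the abstract lists what was collected for the evaluation. For residents, and likewise for relatives, the list includes how satisfied they are with the care given. For staff it reads "team members (satisfaction with job, ability to provide person centered care, team relationships". Satisfaction thus appears for each of the three groups.

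The Aims include "and the association between the level of implementation fidelity and outcomes", and the heading of Objective 3 repeats this. The text under that heading describes every outcome indicator at each time point. It names no instrument to be left out when fidelity is related to outcomes.

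The Data collection section refers process and outcome data together to Table 2 and does not mark which measure serves which purpose. For the team, the only satisfaction measure it names is job satisfaction. For residents and families it names satisfaction with the NTD programme.

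**The concern.** Two separate problems follow.

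The first is validity. Whether residents, relatives or staff are content does not show whether training sessions took place or whether teams worked as the programme prescribes. A home can be well liked for reasons unrelated to NTD, and a home that delivered NTD in full can have dissatisfied staff. Counting satisfaction as evidence of delivery blurs a measure that Objective 1 itself defines as delivery.

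The second is circularity. If a survey contributes to the level of fidelity and is then analysed as an outcome, the two share a component and correlate even if NTD does nothing.

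The stakes are higher than usual because the Design section describes a single group. With no comparison arm, an association between fidelity and outcome is the nearest thing the study has to a dose-response contrast. Readers may take it as evidence that the programme works.

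**Working it through.** The plan gives no figure on this point, so there is nothing to reproduce. The check compares the sections and then illustrates the size.

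**Overlap by group**

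| Group | Source for fidelity (Objective 1) | Satisfaction in the evaluation data (Abstract) | Satisfaction measure in Data collection | Overlap |
|---|---|---|---|---|
| Team members | satisfaction survey | job | job | clear |
| Residents | satisfaction survey | care | the NTD programme | likely, unconfirmed |
| Families | satisfaction survey | care for the relative | the NTD programme | likely, unconfirmed |

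The general surveys and questionnaires in the Objective 1 list also point to Table 2, which holds outcome scales, so the overlap could reach further.

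**Assumptions for the illustration (none is in the document)**

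- Fidelity is the mean of k standardised, independent, equally weighted components.
- One component is satisfaction, and it is also the outcome.
- There is no true relation, and the test is a two-sided Pearson correlation at 0.05.
- k = 4 matches the four kinds of source in Objective 1.
- The number of sites is 6 (Abstract) or 11 (Sample and recruitment).

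**Null correlation.** The correlation of a sum of k independent unit-variance items with one of them is 1/√k:

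- k = 2: 1/√2 = 0.71
- k = 4: 1/√4 = 0.50
- k = 10: 1/√10 = 0.32

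**Unequal weights.** With weight w on satisfaction and the rest shared equally by three other components, r = w / √(w² + (1 − w)²/3):

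- w = 0.10: 0.10/√(0.01 + 0.27) = 0.19
- w = 0.25: 0.50
- w = 0.50: 0.50/√(0.25 + 0.0833) = 0.87

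**Three surveys in one component.** If the satisfaction component averages three independent surveys, each survey correlates 1/√3 with it. The correlation of fidelity with each survey is then 0.50/√3 = 0.29.

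**What r = 0.50 means by site.** t = r√(n − 2)/√(1 − r²):

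- n = 6: 0.50 × 2/√0.75 = 1.15, p about 0.31
- n = 11: 0.50 × 3/√0.75 = 1.73, p about 0.12

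**Simulated null results, k = 4 (50,000 replicates for each number of sites)**

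| Outcome | 6 sites: mean r, rejected | 11 sites: mean r, rejected |
|---|---|---|
| The shared satisfaction survey | 0.46, 17% | 0.48, 37% |
| Correlated 0.3 with satisfaction | 0.14, 6% | 0.14, 7% |
| Unrelated to satisfaction | 0.00, 5% | 0.00, 5% |
| Satisfaction survey, after removing it from fidelity | 0.00, 5% | 0.00, 5% |

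**The case against.** The strongest reply is that the article defines no fidelity score. It has no composite, no weights and no rule for calling a home high or low in fidelity. The sources are to be analysed descriptively, site by site, and two of the four (observation and job enactment) do concern delivery. This stands. It makes every figure above an illustration that depends on the assumed weight. It does not remove the point, because Objective 1 names the satisfaction surveys as fidelity evidence and the Aims require a level of fidelity to relate to outcomes.

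A second reply is that residents' and families' satisfaction with NTD may be a measure of acceptability, distinct from their satisfaction with care. That may be so. The available text of Table 2 stops in the staff rows, so the instruments cannot be matched. The overlap is therefore firm only for team members.

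Three stronger readings are tempting, and the document does not support them.

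- A reader might infer that the whole planned association is an artefact. The outcomes also include falls, infections, acute care admissions, other clinical items, and staff turnover and retention. These are affected only as far as they correlate with satisfaction.
- A reader might take 2112/32 = 66 neighbourhoods as the units. Then r = 0.50 gives t = 0.50 × √64/√0.75 = 4.62, p < 0.0001, and the simulated rejection rate is 99%. Objective 1 analyses fidelity by site, so 6 or 11 is the relevant number.
- A reader might count it as an error that the model text under Objective 3 has no fidelity term. A journal article commonly leaves model terms to the full protocol or analysis plan, so this is not a finding.

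**Conclusion.** The point holds in a limited form. Using satisfaction surveys as evidence of delivery is a stated choice, and it does not fit the article's own definition of fidelity. If the plan is followed as written, the fidelity-outcome association is biased upwards for every survey that serves both purposes. That is clear for team job satisfaction and likely for resident and family satisfaction.

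Under four equal, independent components, a null relation shows as a correlation of 0.50. It is declared significant about 17% of the time with 6 sites and 37% with 11. Weights from 10% to 50% on satisfaction move the correlation from 0.19 to 0.87. For outcomes unrelated to satisfaction the error rate stays at about 5%. For outcomes moderately related to it (0.3), the rate rises only to 6% or 7%.

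These sizes rest on the assumed score. The direction also assumes that higher satisfaction counts as higher fidelity.

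**What to change.** For the fidelity-outcome analysis, base the level of fidelity on the delivery-type sources that Objective 1 already names, structured observations and job enactment. Add session or attendance records if these were kept; the article does not say that they were. Keep the satisfaction surveys as outcomes only.

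If the team wishes to keep satisfaction in the description of implementation, the minimum is a rule that each fidelity-outcome analysis excludes any instrument that also informs fidelity. The rule should also cover the general surveys in the Objective 1 list. It should cover job enactment too, if the work-distribution data described under Objective 3 come from the same source. A short list marking each Table 2 measure as process or outcome would settle the matter, including whether satisfaction with NTD and satisfaction with care are separate instruments.

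The cost is small. The core of the change regroups sources the article already names, and the Data collection section says that analysis is still under way. The downside is fewer indicators of fidelity, and so a less precise measure of it.

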#### Objective 2: exploring contextual factors associated with implementation and outcomes

This objective aims to determine if and how contextual factors might have modified NTD effectiveness. A descriptive analysis of the contextual factors of NTD implementation and outcomes will be conducted: including number and training of NCs, changes in staffing, knowledge and skills required for implementation, physical changes to care environment, and any other events during implementation. Findings of the descriptive analysis will be site specific first. Further investigation of how the NTD model effects were modified by the specific context will be carried out using mixed methods. A qualitative analysis will help in uncovering key contextual factors associated with the implementation and the outcomes and will help to explore emerging themes and patterns in more detail.

#### Objective 3: examine effects of the program on residents, team members, family, and organizational outcomes, and the association between the level of implementation Fidelity and outcomes

The effect of NTD on outcomes will be measured by conducting a descriptive analysis (including mean, standard deviation and frequencies) of all outcome indicators at each data collection point. Mixed models will be conducted on the quantitative data to examine changes in and resident’, family’, and team member’s outcomes variables over time and between groups, while accounting for possible site differences. Qualitative data from the semi-structured interviews will be undergoing a constant comparative analysis. Organizational data will be analyzed by conducting a descriptive analysis on job descriptions and work distribution, skill mix, supportive organizational systems, and staff turnover and retention. Effect of NTD on residents, team members, family, and organization will be described in the context of program.

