## Abstract

**Background:**

As the demand for nursing home (NH) services increases, older adults and their families expect exceptional services. Neighbourhood Team Development (NTD) is a multi-component intervention designed to train team members (staff) in the implementation of resident-centered care in NH settings. A neighbourhood is a 32-resident home area within a NH. This paper presents the protocol used to implement and evaluate NTD. The evaluation aimed to 1) examine fidelity with which the NTD was implemented across NHs; 2) explore contextual factors associated with implementation and outcomes of the NTD; and 3) examine effects of NTD on residents, team members, family, and organizational outcomes, and the association between level of implementation fidelity and outcomes.

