### Sample and recruitment

This study aimed for a rigorous evaluation of the process and complex outcomes of NTD implementation and used a pragmatic real-world effectiveness approach; as such, no formal eligibility criteria or sample size calculations were completed. Data were available from 11 LTC homes, serving 192 residents, which is approximately 2112 residents in total. The number of team members providing direct care varied over time and by LTC home. The sample for the study included residents (*n* = 1110), family members (*n* = 62) and team members (*N* = 2173) of 11 NHs in Ontario, Canada. Given data availability, the power of this study to detect an increase in residents’ self-reported quality of life was based on a one-sample t-test. Assuming an effect size of 0.2, standard deviation of 10, and sample size of 2112, the study will have a power of 0.81 to test change over time. Sample size calculations were performed using SAS University Edition (SAS Institute Inc., North Carolina, USA).

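### Residents are treated as independent in the power basis, and the Objective 3 model names only site although NTD is delivered per neighbourhood, so error control depends on an unstated model form

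*Protocol article*

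**What the plan says.** All references are to the protocol article.

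- **Level of delivery.** Abstract, Background: "A neighbourhood is a 32-resident home area within a NH". Abstract, Methods: "Training was centred in each 32-resident neighbourhood or home area". The Design section says that coordinators run the quarterly team sessions neighbourhood by neighbourhood, and that each coordinator covers two neighbourhoods. Table 1 lists consistent assignment of staff to a neighbourhood as a core belief.
- **Power.** Sample and recruitment says that power to detect an increase in self-reported "quality of life was based on a one-sample t-test", and continues: "Assuming an effect size of 0.2, standard deviation of 10, and sample size of 2112, the study will have a power of 0.81". No ICC, design effect or alpha is given.
- **Sample.** The same section says "Data were available from 11 LTC homes, serving 192 residents" (each, to reach 2112), and then "The sample for the study included residents (*n* = 1110), family members". The Abstract's Methods paragraph gives 6 homes rather than 11.
- **Effect model.** Objective 3 uses mixed models for "outcomes variables over time and between groups, while accounting for possible site differences". It does not say whether site is fixed or random, or whether it acts on level or on change.
- **Multilevel modelling by neighbourhood** appears under Objective 4, which concerns mechanisms.

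**The concern.** Residents of one neighbourhood share a care team, a coordinator, a training schedule and a physical environment. Objective 1 itself expects implementation to vary across neighbourhoods, so residents' changes are likely to be correlated within neighbourhoods and within homes.

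The study has a single group, so change over time is its main quantitative evidence on NTD. The standard error of that change has to reflect variation in change between clusters. A site term that shifts only the level leaves this variation out. The interval is then too narrow and the test rejects too often. A power calculation that treats every resident as independent has the matching fault at the planning stage.

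**Working it through.** **1. The plan's own power figure.** One-sample t-test, n = 2112, two-sided alpha 0.05 (assumed; not stated). Power = P(|T| > t₀.₉₇₅), where T is noncentral t with noncentrality d√n.
- 0.2 as a standardised effect: d√n = 0.2 × √2112 = 9.19, power above 0.999.
- 0.2 as a raw change on SD 10: d = 0.02, d√n = 0.92, power 0.15 (0.23 one-sided).

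Neither gives 0.81. At n = 2112 that power needs d of about 0.062, a raw change of about 0.62 on SD 10.

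**2. Cluster sizes.** 192/32 = 6 neighbourhoods per home; 6 × 11 = 66. With 1110 residents spread evenly (assumed), 1110/66 = 16.8 per neighbourhood and 1110/11 = 100.9 per home.

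**3. Type I error for overall change when site acts on level only.** The layout is 11 homes × 6 neighbourhoods × 17 residents with no true change. The ICCs of change are assumptions, because the article gives none. As a closed-form check, the design effect is DE = 1 + (16.8 − 1) × ICC and the actual error of a nominal 5% test is about 2[1 − Φ(1.96/√DE)].

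| Neighbourhood ICC of change | DE | Closed form | Simulation, site adjusted on level only |
|---|---|---|---|
| 0.02 | 1.32 | 9% | 9% |
| 0.05 | 1.79 | 14% | 16% |
| 0.10 | 2.58 | 22% | 24% |

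The simulation used 3000 runs, so it agrees with the formula to within one or two points. In the same layout, testing the home-level changes on 11 − 1 = 10 degrees of freedom rejects about 5% of the time. Neighbourhoods are nested in homes, so a home-level random effect on change carries their variation for the overall time effect.

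In a second layout, with all 32 residents per neighbourhood and neighbourhood share 0.05, fixed site effects gave 0.23 and a random site effect on change gave 0.05. Adding a home-level share of 0.05 moved these to 0.57 and 0.04.

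**4. Effect of clustering on power, inputs held fixed.** Standardised d = 0.2, n = 1110, effective n = 1110/DE. Home clustering uses DE = 1 + (100.9 − 1) × ICC and 10 degrees of freedom.

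| Home-level ICC | DE | Effective n | Power |
|---|---|---|---|
| 0.01 | 2.00 | 555 | 0.99 |
| 0.02 | 3.00 | 370 | 0.93 |
| 0.03 | 4.00 | 278 | 0.85 |
| 0.05 | 6.00 | 185 | 0.69 |
| 0.10 | 10.99 | 101 | 0.44 |

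Under independence the same inputs give above 0.999. Neighbourhood clustering alone (16.8 per cluster, 65 degrees of freedom) leaves power above 0.999 at ICC 0.02, 0.998 at 0.05 and 0.98 at 0.10. For this effect size, power is therefore sensitive to home-level clustering and hardly at all to neighbourhood clustering.

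**The case against.** **The model may already be sound.** Objective 3 does not say that site is the only level, that it is fixed, or that it acts on level alone. A random site effect on change would control the error, and an article commonly leaves the random-effects structure to the full protocol or SAP. This stands against any claim that the standard errors will be too small; a reader might infer that, but the text does not support it. What remains is that the article names a clustering level which is not the level of delivery, and its wording permits the anti-conservative analysis as readily as the sound one.

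**Neighbourhood is modelled elsewhere.** The latent growth curve model under Objective 4 is multilevel and is to be run per neighbourhood and on the combined data. It serves the mechanism question and does not protect the Objective 3 tests. It does show that the authors recognise the level.

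**Power may not be overstated.** A reader might conclude that 0.81 is too high. The documents do not support this, because 0.81 does not reproduce. On the standardised reading it is too low, and on the raw reading it is too high before any clustering. A home-level ICC of 0.05 with d = 0.2 and n = 2112 happens to give 0.807 (effective n 200, resident-level degrees of freedom), so an unreported allowance for clustering is conceivable, but nothing in the text points to one. The 0.69 in the table comes from one ICC in an assumed range; at 0.01 to 0.03 power is 0.99 to 0.85.

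**Differences between sites.** Leaving out neighbourhood would also distort a test of whether change differs between sites. Objective 3 states no such test explicitly, and the groups it mentions are undefined, so this is not part of the argument.

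**Conclusion.** The point holds in conditional form. The power basis makes no stated allowance for clustering, and the effect model names site but not the neighbourhood at which NTD is delivered. If site acts on level only, a nominal 5% test of overall change runs at about 9% to 24% over assumed neighbourhood ICCs of 0.02 to 0.10, and higher if homes also differ in their change. If site enters as a random effect on change with small-sample degrees of freedom, the error stays near 5%.

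On power, the supported conclusion is comparative: for any given inputs, ignoring positive clustering gives too favourable a figure. How much too favourable depends mainly on the home-level ICC, which the article does not give. No direction can be assigned to the error in 0.81.

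All sizes assume 11 homes, six equal neighbourhoods per home, 1110 residents spread evenly and two-sided alpha 0.05. If the number of homes is 6, the home-level test has 5 degrees of freedom instead of 10.

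**What to change.** 1. **Objective 3 model.** State resident random effects plus random intercepts and random time slopes for home and for neighbourhood within home, with Kenward-Roger or Satterthwaite degrees of freedom. If the neighbourhood slope cannot be estimated, keep at least the home-level random slope, which is what protects the test of overall change.
2. **Power.** Restate power, or the detectable change, giving the scale of the 0.2, the alpha and sidedness, the analysed number of residents (1110 or 2112) and a design effect over a stated ICC range, for example 0.01 to 0.10 at home level.
3. **Number of homes.** Reconcile the 6 in the Abstract with the 11 in Sample and recruitment, since this sets the cluster count and the degrees of freedom.

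The cost is a sentence or two of analysis text and one recalculation. Table 2 already records unit for residents at every assessment, and the article describes analysis as ongoing, so no new data are needed. The downside is wider intervals and possibly a less favourable power figure.
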